### Statistical Procedure and Data Analysis

Quantitative statistical analyses will be performed using SPSS (versions 27.0 and 28.0; IBM Corp) [60,61] and R package [62]. To investigate the normal data distributions of the dependent variables, ranges of skewness and kurtosis will be determined. The Kolmogorov-Smirnov and the Shapiro-Wilk tests will also be performed to evaluate the statistical significance (mean, 95% CI) and normality of the distributions. In addition, Cronbach α will be assessed for each self-report questionnaire’s subscales. To explore sociodemographic features, frequencies, means, and SDs will be measured.

To examine differences between and within subjects, the 3 groups will be evaluated by a repeated-measures ANOVA for mixed designs, where individuals will be the random effect, while the type of intervention and time (T0/T1/T2/before and after each session) will be the fixed effects. The Akaike information criterion and binary logistic regression will be performed to explore significant influence factors.

Spearman rank correlation coefficient will be used to investigate the relationship between the self-reported measures and heart rate.

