### Study Overview and Objectives

The purposes of the present research project are as follows:

Investigating if PMRT associated with a personalized relaxing scenario in VR can facilitate relaxation and lower state anxietyUnderstanding if the VR scenario helps recall the relaxing image assessed during the follow-up sessionInvestigating if VR is more effective in promoting the association between the relaxing scenario and PMRT than the standard procedure, consisting of PMRT associated with the imagery-induced exposure to a subjective relaxing environmentAnalyzing if the relaxing sessions administered via Zoom are more effective in managing anxiety and stress than a procedure administered via audio-tracks.

We hypothesize that VR would be more effective than GI in promoting relaxation and decreasing state anxiety because it would facilitate the visualization process, allowing individuals to have more realistic sensory experiences than imagery-induced exposure.

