### Study Design

The present protocol of the proof-of-concept study is a longitudinal, between-subjects, 3-armed randomized controlled trial aiming to compare three treatment conditions (Figure 1):

Active Comparator condition, consisting of the deployment of the PMRT training via Zoom and GI exposure. It consists of a standard behavioral intervention based on 4 individual PMRT sessions via Zoom (t1-t4), an in vivo PMRT relaxing session and GI conducted by a psychotherapist (T1) after a week from the baseline assessment (T0), and a follow-up phase (T2) after 2 weeks consisting in recovering the GI relaxing scenario and PMRT session (see Multimedia Appendix 1 and Figure 2).Intervention A is an experimental condition in which the complementary intervention is composed of the PMRT administered via Zoom integrated with a personalized VR exposure deployed by a head-mounted display (Oculus Quest 2). It comprises 4 individual PMRT sessions via Zoom (t1-t4), an in vivo PMRT relaxing session and VR exposure (T1) after a week from T0, and a follow-up phase that consists of the same activities as the Active Comparator condition (see Multimedia Appendix 1 and Figure 3).Intervention B is an experimental condition in which the complementary intervention is composed of progressive muscle relaxation training administered through an audio-track integrated with the same personalized VR exposure setup in Intervention A. It is composed of 4 individual PMRT sessions via an audio-track delivered on the Moodle platform (t1-t4), an in vivo PMRT relaxing session and VR exposure (T1) after a week from T0, and a follow-up phase that consists of the same activities as the Active Comparator and the Intervention A conditions (see Multimedia Appendix 1 and Figure 4).

The assessment phases take place at baseline (T0), before and after the 4 PMRT sessions (via Zoom or audio-track), at the fifth in-presence session (T1), and a week later (T2).

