The T0 (baseline) assessment phase has a duration of approximately 37 minutes, is the same for all participants, and is administered at the Virtual Reality Laboratory (A10-A11), Department of General Psychology, University of Padova (Italy). In this phase, the following measures are administered: (1) a demographic schedule (addressing age, gender, nationality, mother tongue, marital status, years of school attendance, employment status, psychological problems or disorders, ongoing psychological treatment, drug use, medical conditions, neuromuscular issues, previous injures, previous experiences in relaxation practice or anxiety management training, or with Oculus), and also, refraining from smoking, intense physical exercise, consuming caffeine for at least 1 hour before testing, and consuming alcohol for at least 6 hours before testing [42]; (2) a series of self-report questionnaires investigating depression, anxiety, stress, quality of life, and distress coping strategies (State Trait Anxiety Inventory-Y [STAI-Y], Depression Anxiety Stress Scales-21 [DASS-21], Psychological General Well-Being Index [PGWBI], and COPE-NVI); and (3) resting heart rate detection with an Mi Band 2 sensor.

Before and after each relaxation session (t1-t4), in approximately 20 minutes, the personal level of tension is assessed by using a visual analog scale from 0 (no tension) to 10 (extreme tension level). The state-anxiety level is evaluated based on the STAI-Y1. The 4 relaxation sessions are administered 2 to 3 days apart from each other for all 3 groups. The assessment phase is administered through Moodle, an e-learning platform used for data collection.

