### Power Calculation

Sample size estimation was computed with G*Power 3.1 software (Heinrich Heine Universität Düsseldorf) [43]. As a statistical test, the repeated-measures ANOVAs between factors have been considered. The effect size was set as 0.25, the α as .05, and the Power (1β error probability) as 0.80. We have 3 separate groups and 3 measurements. On the basis of these parameters, we estimated having to recruit at least 36 participants for each of the 3 groups.

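### For state anxiety and tension before the T1 session, the Zoom-versus-audio objective should be tested by one planned 1-df contrast of both Zoom arms against the audio arm, not only by the three-group F test.

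*Protocol article*

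**What the plan says.** All places are in the Protocol article.

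- **Objective** (Study Overview and Objectives): one stated aim is to see whether "relaxing sessions administered via Zoom are more effective in managing anxiety and stress than a procedure administered via audio-tracks". The abstract presents this as a secondary aim.
- **Arms** (Study Design): of the Active Comparator, "It consists of a standard behavioral intervention based on 4 individual PMRT sessions via Zoom (t1-t4"). Of Intervention A, "It comprises 4 individual PMRT sessions via Zoom (t1-t4"). Intervention B has four audio-track sessions on Moodle instead. At T1 the Active Comparator adds guided imagery (GI), and Interventions A and B add the same VR set-up.
- **Measurements** (Study Design): tension is rated before and after each of t1-t4, and "The state-anxiety level is evaluated based on the STAI-Y1". Both are recorded again before and after the T1 and T2 sessions. DASS-21, which holds the stress subscale, is given at T0, after the T1 session and after the T2 session, but not at t1-t4.
- **Analysis** (Statistical Procedure and Data Analysis): "the 3 groups will be evaluated by a repeated-measures ANOVA for mixed designs, where individuals will be the random effect", with type of intervention and time as fixed effects. Time includes the readings before and after each session. No contrast is named for Zoom versus audio.
- **Sample size** (Power Calculation): the calculation rests on the between-groups test of a repeated-measures ANOVA, for three arms and three occasions. Its settings read: "The effect size was set as 0.25, the α as .05, and the Power (1β error probability) as 0.80". The result is at least 36 per group, 108 in all.

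**The concern.** The objective compares two delivery modes, but the stated test compares three arms. Up to the start of T1, two of those arms are treated alike. One of the two degrees of freedom of the group test is therefore spent on a difference that the design gives no reason to expect. A significant three-group F also does not say that Zoom differs from audio, so a further test would be needed to answer the question.

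What is at stake is power for a secondary aim, and clarity about which comparison answers it. If the contrast is not fixed in advance, someone could choose between a pooled-Zoom result and an A-versus-B result after seeing the data. The Results section shows that group comparisons have already been run on an early part of the sample.

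**Working it through.** **Inputs.** From Power Calculation: f = 0.25, alpha = .05, 3 groups, 3 measurements, 36 per group. Assumed, because the article does not give them: correlation between readings ρ = 0.5, two-sided tests, SD = 1 on the analysed scale, exactly 36 per arm, no dropout.

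**1. The plan's own figure.** For the between-groups test, λ = N f² m / (1 + (m − 1)ρ) = 108 × 0.0625 × 3 / 2 = 10.125, on 2 and 105 df. Power is 0.809; N = 105 gives 0.797. So 36 per group reproduces with ρ = 0.5. With ρ = 0.3 or 0.7 the required N would be 87 or 129.

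**2. What f = 0.25 means here.** With both Zoom arms at 0 and audio at d, the SD of the three means is 0.471d. Setting 0.471d = 0.25 gives d = 0.53.

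**3. Noncentrality for a single reading.**
- Three-group F: λ = 108 × (0.471d)² = 24d², on 2 df.
- Contrast, mean of both Zoom arms versus audio: variance 1/72 + 1/36 = 1/24, so λ = 24d², on 1 df.
- Pairwise A versus B: variance 1/36 + 1/36 = 1/18, so λ = 18d², on 1 df.

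The F test and the contrast use the same 108 people and carry the same signal. The contrast gains because it does not spend a second degree of freedom. The pairwise test has less signal: its standard error is 0.236, against 0.204 for the contrast.

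**4. Power for a single reading.**

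| d | Three-group F | Contrast 72 v 36 | Gain over F (points) | Pairwise 36 v 36 |
|---|---|---|---|---|
| 0.40 | 0.39 | 0.49 | 10 | 0.39 |
| 0.53 | 0.63 | 0.73 | 10.5 | 0.60 |
| 0.60 | 0.74 | 0.83 | 9 | 0.71 |

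**5. Several readings averaged.** The variance is multiplied by (1 + (m − 1)ρ)/m. With ρ = 0.5 this is 0.667 for m = 3 and 0.5625 for m = 8. Eight readings fall after delivery has begun and before the Zoom arms diverge: one after t1, two each at t2, t3 and t4, and one before T1 (1 + 6 + 1 = 8). The t1 pre-session reading precedes any training.

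| d | m | Three-group F | Contrast | Gain (points) |
|---|---|---|---|---|
| 0.53 | 3 | 0.81 | 0.88 | 7.5 |
| 0.53 | 8 | 0.87 | 0.93 | about 6 |
| 0.40 | 3 | 0.55 | 0.66 | 11 |
| 0.40 | 8 | 0.63 | 0.735 | 10.5 |

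For m = 8 and d = 0.53, the gain is about 2 points at ρ = 0.3 and 8.5 at ρ = 0.7.

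**6. Why pooling must stop at T1.** After the T1 session one Zoom arm has had GI and the other VR, while the audio arm has had VR. With no delivery effect at all, the pooled contrast would be off by half the VR-GI difference. The preliminary T1 means in Results (39.35 for GI, 30.10 for VR) differ by 9.25, so the bias would be 4.6 STAI points. With VR-GI effects of 0.5 or 0.8 SD, the pooled contrast would reject a true null about 23% or 49% of the time.

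**The case against.** The strongest reply is that the plan excludes nothing. A three-level arm factor can carry the 1-df contrast, follow-up contrasts are often left to an analysis plan, and only a condensed article is shown. That stands as far as omission goes: an unnamed contrast is not in itself an error. The point here is an improvement on the test that the article does state for this objective.

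A reader might infer that the audio arm will be compared with only 36 Zoom participants, and so with about two thirds of the relevant data. The article does not say so. It names no A-versus-B test, and its three-group F uses all 108. The 36 v 36 column above shows only what such a follow-up would give if it were chosen. The largest loss that could be quoted, about 13 points, is the gap between that pairwise test and the contrast, so it cannot be charged to the stated analysis.

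A reader might also take the Zoom arms to be identically treated throughout. They are alike only up to the T1 pre-session reading. The objective also names stress, but DASS-21 is never given at t1-t4, so the gain reaches state anxiety and tension only.

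Nor does a chance difference between the two like-treated Zoom arms inflate the error rate of the F test. That is ordinary type I error, held at .05. The difficulty is only that such a result would not answer the Zoom-versus-audio question.

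Finally, pooling assumes that knowing one will receive VR does not change responses before T1. The article does not say when participants learn their arm, so this reservation stands and calls for a check.

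**Conclusion.** The point holds in a limited form. For STAI-Y1 and tension up to the T1 pre-session reading, a pre-stated 1-df contrast of both Zoom arms with the audio arm is better focused and more powerful than the three-group F test. The gain is about 9 to 10.5 points for a single reading at d = 0.4 to 0.6. With readings averaged at ρ = 0.5, it is about 6 to 7.5 points at d = 0.53 and 10 to 11 at d = 0.4. These sizes rest on equal means in the two Zoom arms, 36 per arm, no dropout, and an assumed correlation. The article gives no effect size for this particular comparison, so d = 0.53 is the trial-wide f = 0.25 translated to this pattern of means. This is a low-cost improvement to a secondary aim of a pilot study and does not invalidate the planned model.

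**What to change.** In Statistical Procedure and Data Analysis, keep the three-arm model and add:

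- For STAI-Y1 and tension from t1 to the T1 pre-session reading, the Zoom-versus-audio objective is tested by one planned 1-df contrast: the mean of the Active Comparator and Intervention A versus Intervention B. The reading before the t1 session precedes training and carries no delivery effect.
- From the T1 post-session reading onward, and for DASS-21 stress, the arms stay separate and Intervention A versus Intervention B is the delivery contrast.
- A versus B at t1-t4 is reported as a sensitivity check on whether expecting VR affects responses before T1.

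The cost is a few sentences, with no new data or participants. Because early comparisons have already been run, the text should be dated and should state what had been seen by then.

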**Methods:**

Based on a longitudinal, between-subject design, 108 university students will be randomly exposed to one of three experimental conditions: (1) PMRT via Zoom and GI exposure, (2) PMRT via Zoom and personalized VR exposure, and (3) PMRT based on audio-track guidance and personalized VR exposure. Individuals are assessed before and after 7 training sessions based on self-report questionnaires investigating anxiety, depression, quality of life, coping strategies, sense of presence, engagement, and side effects related to VR exposure. Heart rate data are also detected by an Mi Band 2 sensor.

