## Methods

### Ethics Approval

This study protocol involving human participants was General Data Protection Regulation compliant and developed following the Declaration of Helsinki (Italian law 196/2003, European Union General Data Protection Regulation 679/2016). The institutional review board of the Interdepartmental Ethical Committee of Psychology (17 Area) of the University of Padova (Italy) approved the study protocol on May 28, 2021 (approval number 4213). In February 2022, the trial was tested based on a convenience sample of 5 individual volunteers from the general population. Then, it was decided to introduce the following questionnaires: the Coping Orientation to the Problems Experienced-New Italian Version (COPE-NVI), the ITC-Sense of Presence Inventory (ITC-SOPI), the Vividness of Visual Imagery Questionnaire [37,38], and the Test of Visual Imagery Control [37,38]. The amendments and supplementations have been accepted, and the protocol received the final approval of the institutional review board of the Interdepartmental Ethical Committee of Psychology (17 Area) of the University of Padova, Italy (approval number 4701; April 29, 2022). Before their study enrollment, the participants signed a written informed consent form based on a paper-and-pencil form, agreeing to participate in all the study sessions.

They were informed that (1) their data would be confidential, (2) they could omit any information they did not wish to give, and (3) they could withdraw from the study without providing any explanation.

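### The named repeated-measures ANOVA, in its usual form, would exclude participants with a missing occasion, and a target of exactly 3 x 36 leaves the stated 0.80 power unprotected

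*Protocol article*

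**What the plan says.** All places are in the Protocol article.

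- **Statistical Procedure and Data Analysis:** "the 3 groups will be evaluated by a repeated-measures ANOVA for mixed designs, where individuals will be the random effect". Intervention type and time are the fixed effects, and time covers T0, T1, T2 and the assessments before and after each session. SPSS and R are both listed. No procedure or estimation method is named.
- **Power Calculation:** for the choice of test, "the repeated-measures ANOVAs between factors have been considered". The inputs are f = 0.25, alpha 0.05 and power 0.80, for three arms measured three times. The result is that "we estimated having to recruit at least 36 participants for each of the 3 groups".
- **Abstract, Methods:** "108 university students will be randomly exposed to one of three experimental conditions".
- **Ethics Approval:** participants were told that "they could omit any information they did not wish to give" and that they could withdraw without giving a reason.
- **The Integrated PMRT and Virtual Environment Design:** in Intervention B the first four sessions are self-managed on Moodle. In the other two arms a psychotherapist conducts them over Zoom.
- **Results:** the preliminary VR versus GI comparisons of state anxiety at T1 and T2 were computed as repeated-measures multivariate ANOVAs.

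**The concern.** A classical or multivariate repeated-measures ANOVA needs a complete response vector for each person. A participant who misses one of the occasions in the model contributes nothing, even if all other forms were completed. The analysis then compares completers rather than the randomised groups.

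Two things are at stake. The first is power: the number to be randomised equals the number the calculation needs, so any exclusion counts directly against the stated 0.80. The second is the randomised comparison itself. Zoom versus audio delivery is one of the trial's stated aims, and eight of the 13 STAI-Y1 forms fall in the t1-t4 sessions, where the audio arm works alone and the Zoom arms have a therapist present. If completion differed between the two modes, exclusion would be uneven in exactly that contrast.

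**Working it through.** **1. Reproduce the stated sample size.** Inputs from Power Calculation: f = 0.25, alpha = 0.05, power 0.80, k = 3 groups, m = 3 measurements. The correlation between measurements (rho) is not stated; 0.5 is assumed. For the between-factors test:

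lambda = f² × N × m / (1 + (m − 1) × rho), with df = (k − 1, N − k).

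At N = 108: lambda = 0.0625 × 108 × 3 / 2 = 10.125, df = (2, 105), power 0.809. The next smaller balanced total, 105, gives 0.797. So 108 is the smallest balanced total that reaches 0.80, and the plan's 36 per group is reproduced. Other values of rho do not return 108: 0.4 needs 96 and 0.6 needs 117.

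**2. Reserve.** 3 × 36 = 108 is both the calculated and the randomised number. The listed inputs contain no attrition term.

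**3. Power if participants are excluded, three measurements, rho 0.5.** The loss rates are assumptions; the document gives none.

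| Loss | Analysed | Power |
|---|---|---|
| 0% | 108 | 0.809 |
| about 3% | 105 | 0.797 |
| 5% | 103 | 0.788 |
| 10% | 97 | 0.761 |
| 15% | 92 | 0.737 |
| 20% | 86 | 0.704 |

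**4. Count the occasions for STAI-Y1.** T0 (1) + t1-t4 before and after (4 × 2 = 8) + T1 before and after (2) + T2 before and after (2) = 13. Most other outcomes in Table 1 have three phases or fewer.

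**5. Participants lost under complete-case analysis.** If forms go missing independently with probability p, the share with at least one missing is 1 − (1 − p)^m.

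| p per form | Lost, 3 occasions | Lost, 13 occasions |
|---|---|---|
| 1% | 3.0% | 12.2% |
| 2% | 5.9% | 23.1% |
| 3% | 8.7% | 32.7% |
| 5% | 14.3% | 48.7% |

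**6. Match each loss to its own design.** With 13 occasions, the same f and rho 0.5, lambda at N = 108 is 0.0625 × 108 × 13 / 7 = 12.54 and power is 0.888. It is 0.805 at 87 complete cases and 0.7996 at 86. Solving 1 − (n/108)^(1/13) gives 1.65% missing per form for n = 87 and 1.74% for n = 86.

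At 3% missing per form, 13 occasions leave 73 complete cases and power 0.724; three occasions leave 99 and power 0.770. Putting the 13-occasion loss (n = 73) into the three-measurement formula would give 0.625, but that mixes two designs and should not be used.

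**The case against.** The strongest objection is that the article never says incomplete cases are excluded. It makes individuals a random effect and intervention and time fixed effects, which is also how a likelihood mixed model is described, and both named packages can fit one. A reader might infer that the plan drops anyone with a single missing form; the text does not support that as a statement of what will be done. What remains is that repeated-measures ANOVA is named in two sections, and that the only implementation shown, in the Results, is the multivariate form.

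A reader might also infer that all 13 STAI-Y1 occasions enter one model. No section says so. Table 1 frames state anxiety as change from baseline to T1 and T2, and the power calculation uses three measurements. The 13-occasion figures are therefore an upper case. Independence is also unfavourable: withdrawal clusters missing forms in the same people, so a given rate per form then loses fewer participants.

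A reader might further infer that the Zoom versus audio comparison is biased. No missingness by arm is reported, every arm completes its forms on Moodle, and an omitted answer is not a missing form.

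The 0.80 refers to the between-groups test. Under the same nominal f and rho, the group-by-time interaction with three measurements still has 0.96 power at 55 participants. The loss of power shown here is that of the test the plan chose for sizing.

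Finally, missing-data rules and analysis sets are commonly left to an analysis plan, and their absence is not the point made here. The point is the method that is named, combined with a target that has no margin.

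**Conclusion.** The point holds in conditional form. If the named ANOVA is fitted in its usual form, participants with a missing occasion are excluded, and neither the stated power nor the randomised comparison is protected.

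With three measurements and rho 0.5, losing three of 108 participants takes power just below 0.80, and losing 10% takes it to 0.761. That is a modest shortfall at low loss. If all 13 STAI-Y1 occasions were analysed, power would start higher and fall below 0.80 only above roughly 1.6 to 1.7% missing per form under independence.

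These figures rest on an assumed correlation, chosen because it reproduces 108, and on assumed loss rates. Bias between arms is a risk that the design makes plausible, not something the document shows. The change is worth making because it costs almost nothing, and nothing at all if a mixed model was already intended.

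**What to change.** In Statistical Procedure and Data Analysis, state that the group comparison uses a linear mixed model fitted by REML to all available observations of all randomised participants. It should include arm, visit and arm-by-visit, the T0 value as covariate where the outcome is collected at T0, and T1 and T2 as the target visits.

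In Power Calculation, state the assumed correlation and restate the power at the number expected to be analysed.

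The cost is one changed sentence in the analysis section and a slightly less favourable power figure. SPSS and R both fit the model, and no extra participants are needed. The model keeps partial records and relies on data being missing at random; it does not remove bias if missingness depends on unobserved values.
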